#### 2. Patient-Specific Functional Scale

The Patient Specific Functional Scale assesses individual disabilities in a short, efficient format, and was designed to complement generic or condition-specific measures [13]. It has been shown to have excellent test-retest reliability and sensitivity, and good validity in individuals with knee dysfunction [13]. Participants are asked to nominate up to 5 functional activities that they are experiencing difficulty with. The current level of difficulty associated with each activity due to the specified condition is then rated on an 11-point scale, where 0 is "unable to perform the activity" and 10 is "able to perform activity at same level as before injury or problem", and the average score across all activities is calculated.

#### 3. McGill Pain Questionnaire

The most commonly used multidimensional pain measure, the McGill Pain Questionnaire provides a description of the participant's pain experience, and has been utilised as a primary outcome measure in previous knee pain studies [21,22]. The first component involves descriptors of pain categorised as sensory, affective, evaluative and miscellaneous. Twenty groups of words are presented, with the participant required to select one word from each group that best describes their pain. The word chosen is scored by its rank order within the group, with the first word scoring 1, the second word scoring 2, and so forth. If no words are applicable a score of zero is recorded for that group. The Pain Rating Index is the sum of the scores across the 20 groups (range 0–78). The Number of Words Chosen is the number of groups for which a word was selected (out of 20). The second component is the Present Pain Index, a six point scale of severity ranging from no pain (0) to excruciating (5). For the final component, the participant selects one of three groups of words that best describes the pattern of their knee pain, or how pain changes with time, and leaves the question blank if there is no pain.

#### 4. Medical Outcomes Study 36-Item Short-Form Health Survey

This questionnaire is a widely-used generic measure of health-related quality of life [23], and has been previously used in PFP populations [10]. Thirty-six items are used to calculate eight multi-item scores: physical functioning, role limitations due to physical health problems, bodily pain, general health, vitality (energy/fatigue), social functioning, role limitations due to emotional problems, and mental health.

#### 5. Hospital Anxiety and Depression Scale

This 14-item scale will be used to investigate whether there is an association between PFP and emotional state, and has been found to be a reliable instrument for detection of anxiety and depression in an outpatient setting and a valid indicator of severity [24], and has been used in a previous study of physiotherapy in PFP [17]. Participants are required to select the best of 4 responses to questions pertaining to either anxiety or depression (7 questions each), which are scored from 0 to 3. The scores for the anxiety and depression questions are summed separately to give total scores for each component, where 0–7 represents no anxiety or depression, 8–10 is borderline, and 11–21 indicates the presence of an anxious or depressive state.

#### 6. Physical Activity Level in the Previous Week

Participants' physical activity levels will be quantified using a physical activity questionnaire by which occupational, household and leisure activities of varying intensities can be accurately and reliably measured [25]. This questionnaire involves calculation of the time spent in each of these activity types at moderate, hard and very hard intensities over the preceding 7 days. The total time in hours for each intensity of activity is then multiplied by the metabolic equivalents of the activities (METs, kcal/kg/hour), and summed to give an overall caloric output for the week, and divided by seven to give an average daily output. This can then be standardised to body weight to provide an index that can be compared between and within individuals across time [25]. This questionnaire has been shown to have moderate to high reliability on test-retest, especially with moderate and vigorous intensities of activity [25], and has been used previously in a PFP population [10].

#### 7. Step up, step down and squat tests

Three activities that typically provoke PFP will be used as a physical measure of function [10]. Step up and step down tests will be performed on a 25 cm step in a stepping order that continually loads the study knee, while squats will be of full excursion to the point where the fingers touch the floor. A metronome set at 96 beats per minute will be used to standardise the rate of testing. The repetition number on which the first onset of pain occurs, or the first increase in pain where a constant background ache is present, will be recorded, up to a maximum of 25 repetitions.

#### 8. Pressure Pain Threshold (PPT)

Pressure algometry, which has demonstrated reliability [26], will be used to measure PPT at four sites at the knee: (1) the proximal third of the medial border of the tibia; (2) the midpoint of the patella; (3) the distal portion of the rectus femoris muscle, 5 cm superior to the proximal border of the patella; (4) the most palpably tender point around the knee. A digital pressure algometer (Somedic AB, Farsta, Sweden) will measure the pressure applied at a rate of 40 kPa/s to the test site by a rubber-tipped probe (area 1 cm^2^) positioned perpendicular to the skin. The participant will activate a button at the precise moment that the pressure sensation changes to one of pressure and pain, which will signal cessation of pressure application and freeze the pressure reading onscreen for manual recording. Three measures will be taken at each site and the average calculated to represent the final value.

A further questionnaire regarding any adverse reactions to the intervention and whether any other treatment was sought will be completed at 12 months.

All participants will be required to maintain a daily diary over the 12 month period, recording activity levels, problems with the intervention, analgesia requirements and compliance with the home exercise program. Visual analogue scales for usual and worst pain over a week period will also be recorded.

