### Eligibility criteria

Volunteers will be eligible for participation in the study on the basis of the following criteria: (1) anterior or retropatellar knee pain of non-traumatic origin and greater than six weeks duration that is provoked by at least two of the following activities: prolonged sitting or kneeling, squatting, jogging or running, hopping, jumping, or stair ascending/descending; (2) the presence of pain on palpation of the patellar facets, on step down from a 25 cm step, or during a double leg squat; and (3) pain over the previous week equal to or greater than 30 mm on a 100 mm visual analogue scale. Due to the nature of the outcome measures to be used, participants will require an acceptable understanding of written and spoken English. An ability and willingness to attend all sessions required for completion of the study and comply with intervention protocols for the 12 month study period will also be an essential criterion. Volunteers will be excluded if they have any of the following: (1) concomitant injury or pathology of other knee structures (e.g. menisci, collateral and cruciate ligaments, patellar tendon, iliotibial band, pes anserinus); (2) a history of knee surgery, patellofemoral dislocation or sublaxation, Osgood-Schlatter's disease or Sinding-Larsen-Johanssen syndrome; (3) a positive patellar apprehension test; evidence of knee joint effusion; (4) any foot condition that may preclude the use of foot orthoses; (5) pain in and/or referred from the hip or lumbar spine; or (6) a known allergy to rigid strapping tape. Prior treatment with foot orthoses will also preclude volunteers from participating in order to facilitate blinding as to the differences between the foot orthoses and flat insoles, as will prior physiotherapy treatment for PFP within 12 months of entry into the study and current use of anti-inflammatories or corticosteroids. All participants will be required to be a minimum of 18 years of age for consent purposes, and a maximum of 40 years in order to minimise the likelihood of degenerative joint changes.

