#### 2. Flat inserts

This condition will act as a control for the application of inserts into the footwear, and will likely account for some of the potential placebo effects of prescribing an in-shoe device. The flat inserts will be identical in initial appearance to the foot orthoses described above, made from the same EVA with identical covering fabric and company logo. However, this device will be of uniform thickness along its length (3 mm) and have no inbuilt arch or varus wedging. The only modification that will be made to this insert is gentle heat moulding over the six appointments. Participants will be taught a home exercise program of minimal balance training, slowly progressing from standing on one leg while holding a rail for support, to unsupported single leg stance, moving toes up and down, and with eyes closed. The exercise program will not be reinforced as with the other interventions.

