## Discussion

In order to determine the clinical efficacy and cost-effectiveness of foot orthoses in the management of PFP, a pragmatic randomised clinical trial is to be conducted. Based on the Delphi List of criteria for quality assessment of RCTs [29], particular methodological factors have been incorporated into the study design to minimise bias and optimise the rigor of the RCT. Firstly, participants will be randomly allocated to intervention groups via concealed allocation. Poor allocation concealment has been shown to be associated with bias in RCTs [30]. Secondly, the investigator responsible for assessment of outcome at each time point will remain blind to participants' group allocation. Although it could be argued that the use of self-reported primary outcome measures may itself reduce bias associated with an unblinded assessor, blinding of outcome assessors is still an important component due to the potential for transfer of attitudes regarding an intervention from the assessor to the participant [31]. In this study, blinding of participants and the physiotherapists administering treatment is not possible due to the nature of the interventions used. However, as it has been recommended that greater credence should be placed in results where at least the investigators have been blinded to group allocation [31], the single-blind nature of this study is not deemed to be a methodological flaw. Thirdly, the investigators responsible for statistical analysis will be blind to the treatment group allocation, thereby minimising the likelihood of bias associated with their anticipated outcomes. Fourthly, the data analysis will proceed on an intention-to-treat basis, which amongst other things, maintains randomisation, conservatively manages inflation of type I error rate and imitates real life in which it is somewhat likely that not all patients will receive the ideal or intended treatment that has been prescribed.

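### Harms are elicited only as reactions to, or problems with, the intervention, so all-cause event rates by arm are not obtained and harm comparisons are open to differential attribution

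*Protocol article*

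**What the plan says.** The harm records are described in the closing paragraphs of Outcome measures, after the entry on pressure pain threshold. The first is a single questionnaire: "A further questionnaire regarding any adverse reactions to the intervention". It is given once, at 12 months, and also covers other treatment. The second is a diary kept in every arm: "All participants will be required to maintain a daily diary over the 12 month period". Its contents are listed as "recording activity levels, problems with the intervention, analgesia requirements and compliance with the home exercise program". Pain is added to the diary without any causal condition: "Visual analogue scales for usual and worst pain over a week period will also be recorded".

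On blinding, the Discussion states that "blinding of participants and the physiotherapists administering treatment is not possible due to the nature of the interventions used". Two earlier sections point partly the other way for one contrast. Eligibility criteria excludes people who have already used orthoses, "in order to facilitate blinding as to the differences between the foot orthoses and flat insoles", and the section on flat inserts says the two devices look the same at first. That section also gives the role of the flat insert: "This condition will act as a control for the application of inserts into the footwear".

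**The concern.** In the diary list, activity and analgesia are recorded as they occur, but the harm entry carries a causal qualifier. The questionnaire carries the same kind of qualifier. As described, an event enters the harm data only if somebody connects it with the treatment. Because both records are self-reports, that person is most naturally the participant, although the article does not say so.

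Randomisation supports a fair comparison of harms when the same events are counted in the same way in each arm. With attribution as a filter, the observed difference mixes incidence with how much there is to blame, and here the arms differ widely in content:

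- Orthoses: a contoured device refitted over six visits, with twice-daily exercises.
- Physiotherapy: mobilisation, daily taping and a home programme, but no device.
- Combined: both of these, possibly with a seventh visit.
- Flat inserts: a 3 mm insert, gentle heat moulding and light balance exercises that are not reinforced.

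The distortion need not run in one direction. A blister or sore foot has little to be blamed on in the physiotherapy arm and an obvious suspect in the orthosis arm. For skin irritation under tape the position is reversed. Events that nobody links to treatment are lost in every arm.

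**Working it through.** **No harm figure to reproduce.** The article gives no expected harm rate, no attribution share and no harm analysis. The only documented inputs used here are the recruited size (44 per group; 44 × 4 = 176) and the 0.01 significance level under Planned statistical analysis. The rest of the arithmetic illustrates scale under assumptions.

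**What is recorded with and without a causal link**

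| Record | Needs a link to treatment? |
|---|---|
| 12-month questionnaire, adverse reactions | Yes |
| Diary, problems | Yes |
| Diary, analgesia and activity | No |
| Diary, usual and worst pain | No |
| Questionnaire, other treatment sought | No |
| Pain scales at 6, 12 and 52 weeks | No |
| Perceived treatment effect and global effect, both able to show worsening | Direction of change is captured without a separate harm attribution |

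The lower rows cover the study knee well. They do not identify a new skin, foot, hip, back or other-knee event. Analgesia and other treatment are indirect signals and miss minor events.

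**Model.** Let b be the background risk of an event, the same in both arms; a_C and a_T the shares of background events attributed to treatment in the control and active arms; and e the true excess risk in the active arm, assumed fully attributed.

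- Observed control rate = b × a_C
- Observed active rate = b × a_T + e
- Observed difference = b × (a_T − a_C) + e, so the bias is b × (a_T − a_C)

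The bias is zero whenever a_T = a_C, whatever the value of b.

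**Assumed ranges, with no true excess (e = 0).** The chance of a nominally significant result uses the normal approximation with n = 44 per arm: Φ[(d − z·s0)/s1]. Here d is the observed difference, s0 = √(2p̄(1 − p̄)/n) with p̄ the mean of the two rates, and s1 = √((p_T(1 − p_T) + p_C(1 − p_C))/n).

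| b | a_C / a_T | Observed rates, control / active | Spurious difference | Two-sided 0.05 | Two-sided 0.01 |
|---|---|---|---|---|---|
| 10% | 25% / 75% | 2.5% / 7.5% | 5 points | 0.19 | 0.07 |
| 20% | 25% / 75% | 5% / 15% | 10 points | 0.34 | 0.15 |
| 30% | 25% / 75% | 7.5% / 22.5% | 15 points | 0.50 | 0.27 |
| 10% | 50% / 100% | 5% / 10% | 5 points | 0.14 | 0.05 |
| 20% | 50% / 100% | 10% / 20% | 10 points | 0.26 | 0.10 |
| 30% | 50% / 100% | 15% / 30% | 15 points | 0.39 | 0.18 |

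Third row worked at 0.05: p̄ = 0.15, s0 = √(2 × 0.15 × 0.85/44) = 0.0761, s1 = √((0.225 × 0.775 + 0.075 × 0.925)/44) = 0.0744, and (0.15 − 1.96 × 0.0761)/0.0744 ≈ 0.01, so Φ ≈ 0.50. The approximation is rough where expected counts are small: in the first row they are 44 × 0.025 = 1.1 and 44 × 0.075 = 3.3.

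**Opposite direction.** With b = 30%, a_C = 75%, a_T = 25% and a true excess of 10 points, the observed difference is 0.30 × (0.25 − 0.75) + 0.10 = −0.05. A real excess would appear as a small deficit.

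**The case against.** The strongest reply is that this is a condensed article and the forms are not shown. One sentence and a short list may paraphrase instruments that already contain a fixed symptom list. This stands as a limit: the absence of a fuller adverse-event procedure is not a finding, and the point rests only on how the article defines the two items it does describe.

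Second, recording treatment-related reactions is a recognisable choice for inserts, tape and exercise, and no between-arm harm test is specified, so no stated analysis fails. That is true. It lowers the priority but does not make the recorded rates cause-neutral.

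Three stronger readings are tempting, and the document does not support them.

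- A reader might infer that the control arm gives no background information at all. It gives a rate of attributed reactions, because its participants have a device, appointments and exercises and keep the same diary. What is missing is an all-cause rate.
- A reader might infer that harm rates are simply not comparable across arms. That follows only if attribution differs by arm, which is plausible but not shown. Orthoses against flat inserts is the contrast where it is least supported, since masking is intended there, although the Discussion's general statement sits awkwardly with that intention.
- A reader might infer that flares of knee pain go unrecorded when blamed on the condition. The pain scales and the perceived-effect scales already pick up worsening of the study knee in every arm.

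**Conclusion.** The concern holds in a limited form. As described, both harm items depend on a link to the intervention and come from self-report by participants the protocol calls unblindable. All-cause rates by arm are therefore not obtained for events away from the study knee, and between-arm harm comparisons are open to differential attribution. The exposure is greatest where the physiotherapy or combined arm is one side of the comparison.

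The size cannot be derived from the document. Under the assumed inputs above, the bias runs from 0 with equal attribution to 15 percentage points with a 30% background and attribution shares 50 points apart. The conclusion rests on two inferences: that the participant makes the causal judgement, and that the article's phrases reflect what the forms ask. Efficacy analyses are unaffected. This is a low-cost improvement to harm reporting, not a flaw that threatens the trial's main question.

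**What to change.** In the 12-month questionnaire and in the diary's harm entry, ask every arm the same short list of events regardless of cause: for example skin irritation or blister, foot pain, hip or back pain, pain in the other knee, and new injury. Put perceived relation to treatment in a separate follow-up item. Tabulate all events by arm as the main harm table and attributed events as a second table. If the existing forms already work this way, correcting the description in the article is enough.

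All the information now collected is kept, and no visit or staff time is added. The cost is rewording the two items and having more minor, unrelated events to tabulate.

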**Methods/design:**

A randomised single-blinded clinical trial will be conducted to investigate the clinical efficacy and cost effectiveness of foot orthoses in the management of patellofemoral pain syndrome. One hundred and seventy-six participants aged 18–40 with anterior or retropatellar knee pain of non-traumatic origin and at least six weeks duration will be recruited from the greater Brisbane area in Queensland, Australia through print, radio and television advertising. Suitable participants will be randomly allocated to receive either foot orthoses, flat insoles, physiotherapy or a combined intervention of foot orthoses and physiotherapy, and will attend six visits with a physiotherapist over a 6 week period. Outcome will be measured at 6, 12 and 52 weeks using primary outcome measures of usual and worst pain visual analogue scale, patient perceived treatment effect, perceived global effect, the Functional Index Questionnaire, and the Anterior Knee Pain Scale. Secondary outcome measures will include the Lower Extremity Functional Scale, McGill Pain Questionnaire, 36-Item Short-Form Health Survey, Hospital Anxiety and Depression Scale, Patient-Specific Functional Scale, Physical Activity Level in the Previous Week, pressure pain threshold and physical measures of step and squat tests. Cost-effectiveness analysis will be based on treatment effectiveness against resource usage recorded in treatment logs and self-reported diaries.

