### Intervention

Interventions will be administered by one of 17 experienced registered physiotherapists (Physiotherapists Board of Queensland) located throughout the catchment area. All project physiotherapists will have attended two seminars for explanation and discussion of the intervention protocols and training in fitting of foot orthoses. A qualified sports physiotherapist who has extensive experience in the management of PFP with orthotics will conduct these seminars. A comprehensive manual outlining study procedures will be provided to all project physiotherapists.

Participants will attend six 20–60 minute appointments over a six week period (i.e. one session per week), with details of each session recorded by the project physiotherapist in a treatment log. On completion of the six visits, participants will continue with a self-management program for the remainder of the 12 month study period. This will incorporate the home exercise program relevant to their allocated intervention.

The four intervention groups are as follows.

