#### 1. Foot orthoses

Participants assigned to this group will be provided with prefabricated foot orthoses from a commercially available range (Vasyli International). The orthoses are made of ethylene-vinyl acetate (EVA) of high (Shore A 75°), medium (Shore A 60°) or low (Shore A 52°) density, and have an inbuilt arch support and 6° varus wedge as specified by the manufacturer. The range includes four types of orthoses to suit a variety of footwear: full length and three-quarter length (general use); easy fit (a three-quarter length with lateral cut-away for narrower footwear e.g. men's dress shoes); and slim fit (a thin minimally arched orthosis designed for women's dress/court shoes). In order to maximise compliance, orthoses will be fitted to up to four pairs of the participants' shoes, using a standardised iterative procedure based primarily on perceived comfort (Figure 2). The first stage will involve selection of an appropriate device based on the amount of space available in the shoe (Step 1a) and the length of the participant's foot (Step 1b). In the first instance, an orthosis made from the highest density EVA will be used (Step 2). Following this process, if the orthoses are uncomfortable when worn in the shoe, the therapist will review the type, size and density, and then choose an alternative orthosis that does fit comfortably. If the participant is not satisfied with the comfort level of the orthoses, the orthoses will be customised. This will first involve heat moulding as per the manufacturer's instructions (Step 3a). This process involves mildly heating the underside of the orthosis, placing it in the intended shoe and then having the participant stand on it with the foot positioned in its neutral zone for approximately 60 seconds. If the heat moulding process alone fails to optimise comfort, the therapist will sequentially trial the addition of medial wedges of the rear and forefoot and/or a heel raise to the orthoses (Step 3b). The medial rearfoot wedges have a manufacturer specified 2° or 4° of inclination, the forefoot wedges 4° or 6° and the heel raises are 4, 6 or 8 mm thick. The forgoing underscores the primary goal of fitting of the orthoses to achieve a comfortable fit. Once comfort has been achieved, the effect of the orthoses on performance of a functional task will be evaluated. This will involve quantification of the effect of the orthoses on pain-free performance of an activity identified as pain provocative immediately prior to orthosis fitting, such as, step ups, step downs or squats. A substantial increase in the number of pain-free repetitions that can be performed will be regarded as a success. The therapist will modify the orthoses in order to improve the performance of the functional task, but with the fundamental aim of ensuring the orthoses are comfortable. This process of fitting, reviewing and adjusting the orthoses will continue over the six visits. Participants will also be given a home exercise program of foot arch-forming exercises and weight-bearing calf stretches to be performed bilaterally twice daily.

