### Outcome measures

The blinded assessor will repeat the outcome measures following completion of the 6 visits with the physiotherapist at 6 weeks, and then at 12 and 52 weeks to assess the long term outcome of the intervention.

Outcome will be assessed at each time point using measures that have been previously demonstrated as being acceptably reliable and valid indictors of change [11-16] and used in previous high-quality RCTs of PFP [10,17,18]. The primary outcome measures will be as follows.

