### Sample size considerations

Sample size calculations for this study are based on the 100 mm visual analogue scale for usual pain over the past week. The mean difference between baseline and final score for each group will be compared to measure the effectiveness of each intervention. In order to detect a minimal clinically important difference of 15 mm [15,27], assuming a standard deviation of 20 mm [10], a power of 0.80 and alpha level of 0.01, a sample size of 40 participants per group will be required. To account for dropouts, particularly considering the long duration of the study [28], a group size of 44 will be recruited, with a total sample size of 176.

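### The one direct questionnaire on adverse reactions, which is also the only source that names other treatment sought, is given once, at 12 months

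*Protocol article*

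**What the plan says.** The closing paragraphs of Outcome measures, after the pressure pain threshold item, set one form on harms and co-treatment: "A further questionnaire regarding any adverse reactions to the intervention and whether any other treatment was sought will be completed at 12 months". The paragraph that follows adds a diary: "All participants will be required to maintain a daily diary over the 12 month period, recording activity levels, problems with the intervention, analgesia requirements". Home-exercise compliance and pain ratings on a visual analogue scale complete its listed contents.

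Three other places bear on the point:

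- Outcome measures has the blinded assessor see participants "at 6 weeks, and then at 12 and 52 weeks to assess the long term outcome of the intervention".
- Intervention describes six weekly sessions, "with details of each session recorded by the project physiotherapist in a treatment log". For the foot orthoses, "This process of fitting, reviewing and adjusting the orthoses will continue over the six visits".
- The Abstract (Methods/design) bases the cost-effectiveness analysis on "resource usage recorded in treatment logs and self-reported diaries".

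Planned statistical analysis compares the groups at 6, 12 and 52 weeks, using participants with data at each time.

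**The concern.** The supervised sessions, and the daily taping in Table 1, fall in the first six weeks. The direct question about reactions and other treatment comes at week 52. Visits at 6 and 12 weeks already exist, but neither is stated to include that question.

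Two things are at stake.

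- **Timing of co-treatment.** Eligibility criteria excludes physiotherapy for the condition within the previous 12 months and current anti-inflammatory or corticosteroid use, so the plan itself treats co-treatment as something that can distort outcome. After entry, the form as described asks once whether other treatment was sought. If one group sought more outside care than another, the reader of the 6- and 12-week comparisons would want to know whether that happened before those visits.
- **Completeness.** A form given only at the end is missed by those who have left. Taping is used in two of the four groups, so forgotten or missed reactions need not be spread evenly across groups.

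**Working it through.** **1. What each source is stated to record**

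| Source | When | Reactions | Other treatment |
|---|---|---|---|
| Dedicated questionnaire | Once, 12 months | Named | Named |
| Daily diary | Throughout 12 months | Partly: difficulties with the treatment | Analgesia only |
| Treatment log | Each session, about weeks 0 to 6 | Possibly: contents not listed | Not stated |
| Assessor visits | 6, 12 and 52 weeks | Not stated | Not stated |

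The reactions column has entries from the start of the trial. The other-treatment column, apart from analgesia, has one entry, at the end. The weakness is therefore mainly in other treatment.

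**2. Distance between event and question**

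- From the end of the six-week treatment period to the form: 52 − 6 = 46 weeks.
- From the 12-week analysis to the form: 52 − 12 = 40 weeks.

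A yes or no answer covering the whole year cannot by itself be assigned to weeks 0–6, 6–12 or 12–52. It could be only if the form also asks for dates, which the article does not say.

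**3. How many could miss the form**

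Inputs, from Sample size considerations: 40 per group needed, 44 per group recruited, four groups.

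- Plan's total: 4 × 44 = 176, as stated.
- Allowance per group: 44 − 40 = 4.
- Allowance overall: 4 × 4 = 16.
- As a share of those recruited: 16 / 176 = 9.1%.

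This is the number of losses the plan allows for, not a forecast of missing forms. It becomes the number who miss the form only if all 16 leave before 12 months and none is asked at exit.

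**4. Check on the figure of 40**

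The stated inputs are a 15 mm difference, SD 20 mm, power 0.80 and alpha 0.01. I take alpha as two-sided, which agrees with the planned 99% confidence intervals. The normal approximation gives

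n = 2 × (2.576 + 0.842)² × 20² / 15² = 2 × 11.68 × 1.778 = 41.5, rounded up to 42 per group.

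The plan's 40 is within two participants of this, with power of about 0.78 by the same approximation. Nothing in this point depends on the difference.

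**The case against.** The strongest reply is that the paragraph directly after the questionnaire already provides prospective capture. Every participant is asked daily about difficulties with the allocated treatment, and each supervised session is logged. That stands. A reader might infer from the single questionnaire that early reactions depend wholly on a year's recall, or that the 16 possible leavers are never asked about harm. The documents support neither reading. The diary asks participants from the start, and both diary and log could hold data on a participant up to withdrawal. Nor do the documents give any reaction rate, or any departure rate among those who react, so no size can be put on an under-count of harms.

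Secondly, the diary may be wider than its listed contents. The Abstract draws resource use from logs and diaries, and Planned statistical analysis gives an open-ended list of resources that includes medications. This stands in part: outside treatment might be recorded there, but neither place says so, and analgesia is the only co-treatment named in the diary.

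Thirdly, the form's fields, diary return and withdrawal procedures are details that an article commonly leaves to the full protocol. That is fair, and their absence is not the point here. The single 12-month timing, however, is stated in the article as a design choice and can be judged as one.

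Finally, asking about reactions at visits run by the blinded assessor could reveal allocation. That is a real cost, and the change below has to deal with it.

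**Conclusion.** The point holds in a limited form. The only direct questionnaire on adverse reactions, and the only source that names other treatment sought, is given once at 12 months. Reactions are partly covered by the daily diary and possibly by the session log. For other treatment, analgesia aside, a single year-end answer is a weak basis for placing co-treatment before or after the 6- and 12-week analyses. Up to about 16 of 176 participants (9.1%) could miss the form.

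This rests on three assumptions: that the diary records no more co-treatment than the article lists, that the 12-month form asks for no dates, and that losses match the plan's allowance with no completion at exit. If the full protocol shows otherwise on the first two, most of the timing concern falls away. The point is a cheap improvement to data collection. It does not threaten the primary comparisons.

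**What to change.** Give the same short form at the existing 6- and 12-week visits and at withdrawal, as well as at 12 months. Word each one to cover the time since the previous form, so that other treatment falls into an interval that matches the analyses. Have participants complete it themselves and return it to the research assistant, who already handles communication about allocation, so that the blinded assessor does not see it. Report the answers by group together with the diary entries on difficulties with the treatment, and say how the two sources are combined.

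The cost is one extra page at each of two visits that already take place and at withdrawal, a little more burden on participants, and the need to route the page away from the assessor. Treatment, sample size and the planned outcome analyses are unchanged. The change has to be made before follow-up begins, because the timing of other treatment is hard to recover afterwards.
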